### Outcomes and measures

#### General practitioners

GPs will be asked to complete two short pre- and post-intervention questionnaires. The pre-intervention questionnaire will be filled out upon recruitment (BL). The post-intervention questionnaire will be sent by postal mail 12 months after BL. Pre- and post-intervention questionnaires will contain closed questions on referral and counseling behavior of patients with obesity, satisfaction with own knowledge about obesity, attitudes towards obesity as a chronic disease, relevance of different causes of weight gain and attitudes on different aspects of obesity management. Stigma concerning obesity will be assessed using the Fat Phobia Scale (FPS) by Bacon et al. [29]. The FPS consists of 16 pairs of adjectives on a semantic differential. Furthermore, GPs of the intervention group will be asked to evaluate the 5As online tutorial in regards to the relevance of its knowledge contents and its usability within the primary care setting 12 months after intervention completion.

Furthermore GPs will be provided with a list of co-morbid conditions and will be asked to complete this list and assess the weight status for each participating patient at BL and 12 months follow-up.

#### Patients

Patients will be asked to complete three questionnaires at recruitment as well as 6 months and 12 months follow-up, respectively. All three questionnaires will be sent by postal mail. In addition to demographics (gender, age, educational level, working status, marital status), the outcome measures for patients will include patient-doctor interaction regarding obesity management over the past 6 months, quality of life, weight history and BMI, motivation to engage in weight management strategies, self-stigma regarding obesity, the assessment of depressive and anxiety symptoms and personality traits. Instruments for each of the mentioned outcomes are described in the subsections below. As the 5As framework primarily aims to improve weight management counselling by improving the interaction between patients with obesity and their physicians the primary outcome of this study will focus on the patient-doctor interaction. Changes in weight will be assessed as a second outcome after investigating improvements in the patient-doctor interaction regarding weight counselling.

##### Primary outcomes

Patient’s perspective on the *patient-doctor interaction* regarding the management of obesity over the past 6 months will be assessed using an adapted version of the German adaptation of the Patient Assessment of Chronic Illness Care (PACIC) [30, 31]. The PACIC is a 26-item questionnaire scored on a 5-point Likert scale ranging from 1 (= never) to 5 (= always). The first 20 items of the PACIC are arranged into five scales: patient activation, delivery of care, goal setting, problem solving, and follow-up. Further six items of the PACIC cover elements of the original 5As approach (ask, advise, agree, assist, arrange). The 5A PACIC sum score will be calculated according to the scoring instruction by Rosemann et al. [31]. Higher scores indicate a stronger congruency to the 5A approach.

##### Secondary outcomes

*Quality of life* will be assessed using the EQ-5D-5 L [32] which consists of a visual analogue scale to assess health related quality of life on a scale from 0 (= worst health) to 100% (= best health). Additionally, five questions cover health related quality of life and perceived impairments rated on a five-point scale from 0 to 4.

*Weight history* will be assessed at BL including the assessment of the beginning of obesity, the number of previous weight loss attempts and the types of weight loss attempts. The *BMI* will be calculated based on self-reported height and weight. Height will only be determined at the baseline assessment, whereas weight will be assessed at every follow-up. In addition, weight will be assessed through the attending GP at BL and 12 month follow-up. As in previous research, a stable weight is defined not differing more than 5% of the original body weight [33].

The *willingness to engage in weight management strategies* will be measured using the Readiness Ruler adapted from Zimmermann et al. [34] and Stott et al. [35]. The ruler is a visual analogue scale to assess the readiness for change regarding weight loss on a scale from 0 (= not ready to change) to 10 (= ready to change). Additionally, *weight loss intentions and current activities of weight management* will be assessed using the stages of change algorithm adapted from DiClemente and Prochaska [36] and Prochaska et al. [37]. The stages of change algorithm consists of four questions according to which individuals are categorized into four separate categories of change (precontemplation, contemplation, action and maintenance).

*Depressive symptomatology* within the last two weeks will be measured using the German adaptation of the PHQ-9 [38] which comprises 9 items with a four-point response scale from 1 (=not at all present) to 4 (=present almost every day). The sum score of the PHQ-9 allows classifying the severity of the depressive symptomatology into the following categories: no depression, mild depression, pronounced depression and severe depression.

*Self-stigma* will be measured using a German adaptation of the Weight Bias Internalization Scale (WBIS) [39, 40]. The WBIS comprises 11 items and was developed to assess internalized weight bias among individuals with obesity.

##### Other measures/ covariates

To control for potential confounding effects the following measures will be assessed:

*Anxiety symptoms* within the last four weeks will be measured using the GAD-7 [41] which comprises 7 items with a three-point response scale from 1 (=not at all present) to 3 (=present for more than half the days). The sum of the scale allows classifying the severity of anxiety symptoms into: marginal anxiety, mild anxiety, pronounced anxiety and severe anxiety. The *panic syndrome* will be assessed using the panic-syndrome module of the PHQ-D (phq3a-phq4k) [42]. The panic syndrome module comprises 15 items with a yes/no response scale.

*Personality traits* will be assessed using the 10-Item Big Five Inventory (BFI-10) [43] which is an abbreviated version of the BFI-44. The BFI-10 comprises two items for each of the five personality dimensions with a five-point response scale from 1 (=disagree strongly) to 5 (=agree strongly).

Additionally, four half-open questions cover the *counseling experience of patients* within the last six months with their attending GP (“Have you seen your GP within the last six months?”, “How often have you seen your GP within the last six months? Please consider only direct contacts with your GP”, “Has your weight been discussed in the consultation and who took the initiative?”, “Which aspects of weight have been discussed?”).

### Data collection and data management

Data will be collected using questionnaires sent by postal mail including a prepaid return envelope. Monetary incentives (10 Euros per questionnaire) are used to ensure high follow up rates. Double data entry will be used for all questionnaires to keep the rate of data errors very low. Since the trial is based on questionnaires, monitoring is not an issue. The nature of this trial renders a data monitoring and safety board unnecessary. Completeness of the study data and study documents will be audited by the trial manager.

### Data analysis

After completion of the trial data cleaning and quality control will be conducted. Prior to testing the effectiveness of the intervention, appropriate statistical tests will be used to examine possible baseline differences between groups (e.g. age, sex, educational level, employment status and marital status). Hierarchical regression models will be used to analyze treatment effects from baseline to follow up. Models will be adjusted for the baseline outcome value and confounding factors, such as age, sex and socio-economic background. All analyses will be intention-to-treat in order to control for non-random dropout effects. Patterns of missing values will be inspected and, if applicable, replaced using appropriate statistical methods. Additionally, the effect of the intervention on provider knowledge, satisfaction with own knowledge and perceived counseling behavior will be analyzed. The level of statistical significance will be set at *p* < 0.05 for all statistics.

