#### Power calculation and sample size

Based on previous research, a power based sample size calculation was done using Stata 13.1 SE software package (StataCorp LP, College Station, TX). The primary outcome measure, the 5A PACIC sum score, may yield a minimum of 15 points difference prior to post-intervention. With a power of 95% and a standard deviation of 20 points [27], a sample size of *n* = 47 participating patients for each group was estimated to detect group differences. Given a 30% drop-out-rate, which is based on previous work of the ISAP, the overall sample size would comprise *n* = 134. According to Rueda-Clausen et al. [27] 15 points were regarded as a clinical significant change in the 5A PACIC sum score. Taking into account the interclass correlation coefficient of 5% from the cluster randomization the sample size would increase slightly to *n* = 66 patients per group. Given the 30% drop-out-rate *n* = 86 patients were estimated for each group. We estimate that 6–7 patients per practice could be recruited into the trial. Therefore, the trial aims to enroll at least 20 GPs. The overall sample will comprise 172 patients and not less than 20 GPs.

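### Intention-to-treat is wrongly given as the control for non-random drop-out; the other planned steps protect only if data are missing at random

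*Protocol article*

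**What the plan says.** Four statements in the protocol article bear on this point.

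- Data analysis gives intention-to-treat a purpose: "All analyses will be intention-to-treat in order to control for non-random dropout effects".
- The next sentence plans a separate step: "Patterns of missing values will be inspected and, if applicable, replaced using appropriate statistical methods".
- The same section sets the model: "Hierarchical regression models will be used to analyze treatment effects from baseline to follow up". On covariates it says: "Models will be adjusted for the baseline outcome value and confounding factors, such as age, sex and socio-economic background".
- Power calculation and sample size budgets for loss: "Given a 30% drop-out-rate, which is based on previous work of the ISAP, the overall sample size would comprise" 134 patients, before clustering is allowed for.

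The primary outcome is the 5A PACIC sum score, in which patients rate their GP's handling of obesity over the past six months. It is collected by post at baseline, 6 and 12 months. The article limits loss with 10 Euros per questionnaire, prepaid envelopes and postal reminders.

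**The concern.** Intention-to-treat answers one question: in which arm a patient is counted. It keeps patients in the arm of their practice whatever the GP did with the tutorial. It says nothing about the value of a score that was not returned, so it cannot control drop-out related to that score. The article names non-random drop-out as a threat and assigns to it a principle that does not act on it.

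The risk is plausible here. The outcome is the patient's opinion of the GP, and the same patient decides whether to post the form back, so return could depend on the opinion. The intervention aims to change that opinion, so the dependence could differ by arm. At stake is a trial report that follows this sentence and says informative drop-out was controlled when no stated step did so.

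**Working it through.** **Inputs from the article.** Target difference 15 points, SD 20, power 95%, significance level 0.05 (taken as two-sided), drop-out 30%, intracluster correlation 0.05, 6–7 patients per practice, 86 patients per group.

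**Input assumed here.** The gap in mean score between non-responders and responders. The article gives none, so a range is shown.

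**1. The plan's own figures.** Per group, n = 2 × (1.960 + 1.645)² × 20² / 15² = 46.2, rounded up to 47, as stated. With 30% loss, 47 / 0.70 = 67.1 per group, or 134.3 in total; the article states 134. The 30% is therefore a working assumption of the design.

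**2. Is power the problem?** Taking 86 per group as stated, 86 × 0.70 = 60.2 completers. The design effect is 1 + (6 − 1) × 0.05 = 1.25, or 1 + (7 − 1) × 0.05 = 1.30. Power for 15 points is then 95.7% or 95.0%. On these inputs the issue is bias, not power.

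**3. Size of a possible bias.** Let d be the share lost in an arm and g the mean of non-responders minus the mean of responders in that arm (1 = intervention, 0 = control). The full-arm mean is the responder mean plus d × g, so

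bias of the completers-only difference = −(d₁ × g₁ − d₀ × g₀).

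| Loss, intervention / control | Gap, intervention / control | Bias (points) |
|---|---|---|
| 30% / 30% | −10 / −10 | 0 |
| 30% / 30% | −5 / 0 | 0.30 × 5 = 1.5 |
| 30% / 30% | −10 / 0 | 0.30 × 10 = 3.0 |
| 30% / 30% | −20 / 0 | 0.30 × 20 = 6.0 |
| 40% / 20% | −10 / −10 | 0.40 × 10 − 0.20 × 10 = 2.0 |

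A positive bias favours the intervention. With 30% loss in both arms, moving the gap to the control arm alone reverses the sign. A 3-point bias is 3 / 15 = 20% of the target. A one-arm gap of 15 / 0.30 = 50 points would be needed to produce or erase a 15-point effect.

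**4. Effect on the test.** The standard error of the difference is √(2 × 20² × 1.25 / 60.2) = 4.08, or 4.16 with 1.30. If the true effect were zero, a 3-point bias would move the test statistic by about 3 / 4.1 = 0.73. The two-sided 5% false-positive rate would then be about 11%. A 1.5-point bias would give about 6.5%.

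**5. What each planned step can do.**

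- Intention-to-treat sets the arm of analysis and does not enter the bias formula.
- The hierarchical model adjusted for baseline score, age, sex and socio-economic background removes the part of the bias that these variables explain.
- Replacing missing values, by any method that predicts from observed data, likewise rests on the data observed.
- None of the three acts on loss that still depends on the unseen score once the observed data are taken into account.

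**The case against.** The strongest reply is that the clause is a slip in a condensed article and that the plan does more than the clause suggests. Much of this stands.

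- A reader might infer that the plan relies on intention-to-treat alone, leaving the primary estimate unprotected. The document does not support that. A baseline-adjusted hierarchical model and a separate missing-data step are both planned, and either can be valid under missing at random. Incentives, prepaid envelopes and reminders also work to limit loss.
- A reader might infer that the replacement step will be a single imputation that ignores practices. The article does not say so. It speaks of appropriate methods, and the model is hierarchical. An unnamed imputation method is a detail an article may leave to the full protocol or SAP, and it is not counted here.
- A reader might fear that inspecting patterns first lets the method be steered. Randomization and blinding says the analysing statistician does not know the allocation, which leaves little room to favour an arm.
- Patients are blinded to allocation, which makes return that differs by arm less likely. It does not rule it out, because what patients rate is the GP behaviour that the tutorial is meant to change.
- The bias figures describe an unadjusted completers-only comparison, which is not the planned analysis, and the gaps are assumed. Both points are correct. The figures show scale and do not predict a result.

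None of this makes the sentence true. A fuller document may add methods, but intention-to-treat would still not control non-random drop-out.

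**Conclusion.** The point holds as an error in a stated property. Intention-to-treat is credited with controlling non-random drop-out, which it cannot do, and the other steps in the section protect only under missing at random given the modelled variables.

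The possible size is modest: 1.5 to 3 points on a 15-point target for a completers-only comparison. This assumes 30% loss and a gap of 5 to 10 points in one arm only. It is zero if loss and gap are equal in both arms, and adjustment for baseline may reduce it. Bias has not been shown to occur, and it would take an extreme gap to overturn a true 15-point effect. A shift of this size would matter mainly if the true effect were small or absent.

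**What to change.** Replace the sentence on intention-to-treat with:

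> All patients are analysed in the arm to which their practice was randomised. The primary hierarchical model uses all available baseline, 6- and 12-month scores, with random effects for practice and for patient (or a within-patient covariance), and assumes data are missing at random. Robustness to non-random drop-out is examined in a sensitivity analysis that shifts multiply imputed unreturned scores by a pre-stated range (for example 0 to −10 points), separately by arm, with practice in the imputation model.

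The patient-level term is needed. With a practice effect alone, a patient's earlier scores would not properly inform that patient's missing 12-month score, and the missing-at-random statement would fail for drop-out that depends on those scores. The range of 0 to −10 points is an assumption; the trial team should set its own before data are seen. If the full protocol or SAP already holds such an analysis, the sentence can refer to it and only the wording changes.

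The cost is a little extra programming and a more cautious statement about drop-out in the report. Sample size, data collection and the burden on practices do not change.

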#### Intervention costs

The intervention costs will be analyzed considering one-off development costs and running costs for the implementation of the 5A online tutorial. Development costs consisted of labor costs and administrative expenses (license and service fees, technical implementation). Monetary valuation of the labor costs will be based on the collective labor agreement for Federal States (TV-L). Administrative expenses will be documented within the framework of the study. Running costs consist of labor costs for the implementation of the 5A online tutorial by GPs and administrative expenses (technical support, system maintenance and backup). Monetary valuation of the labor costs for GPs will be based on the unit cost for GP contacts and the actual time expenditure of GPs.

#### Power calculation and sample size

Based on previous research, a power based sample size calculation was done using Stata 13.1 SE software package (StataCorp LP, College Station, TX). The primary outcome measure, the 5A PACIC sum score, may yield a minimum of 15 points difference prior to post-intervention. With a power of 95% and a standard deviation of 20 points [27], a sample size of *n* = 47 participating patients for each group was estimated to detect group differences. Given a 30% drop-out-rate, which is based on previous work of the ISAP, the overall sample size would comprise *n* = 134. According to Rueda-Clausen et al. [27] 15 points were regarded as a clinical significant change in the 5A PACIC sum score. Taking into account the interclass correlation coefficient of 5% from the cluster randomization the sample size would increase slightly to *n* = 66 patients per group. Given the 30% drop-out-rate *n* = 86 patients were estimated for each group. We estimate that 6–7 patients per practice could be recruited into the trial. Therefore, the trial aims to enroll at least 20 GPs. The overall sample will comprise 172 patients and not less than 20 GPs.

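### At 30% drop-out the target of 172 does not deliver the stated 66 analysed patients per group, and the 66 does not follow from the stated cluster size

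*Protocol article*

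**What the plan says.** All the figures are in the protocol article, Data analysis, under Power calculation and sample size.

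- **Assumptions:** the primary outcome "may yield a minimum of 15 points difference prior to post-intervention". The calculation is made "With a power of 95% and a standard deviation of 20 points".
- **Before clustering:** "a sample size of *n* = 47 participating patients for each group was estimated to detect group differences".
- **First drop-out step:** for a loss of 30%, "the overall sample size would comprise *n* = 134".
- **Clustering:** with an intraclass correlation of 5%, the requirement becomes 66 per group.
- **Second drop-out step:** for the same 30%, "86 patients were estimated for each group".
- **Cluster size and target:** the article expects 6–7 patients per practice and concludes: "The overall sample will comprise 172 patients and not less than 20 GPs".

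No design effect is stated. The significance level is in the Data analysis section: "The level of statistical significance will be set at *p* < 0.05 for all statistics".

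**The concern.** A drop-out allowance should make the number left after the loss equal the number the calculation requires, which means dividing by one minus the drop-out rate. The paragraph does this when it goes from 94 to 134. When it goes from 66 to 86 it appears to multiply by one plus the rate, which always gives too few. The second step produces the recruitment target.

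The clustering step is also open to question. The design effect depends on the cluster size, and the only cluster size in the article is given after the 66 and does not appear to have produced it. If both points hold, a reader cannot tell which of 66, 86 or 6–7 is meant, or whether the target supports the stated 95% power.

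**Working it through.** **Inputs** (all from Power calculation and sample size, except the significance level, which is from Data analysis): difference 15, SD 20, power 95%, alpha 0.05, ICC 0.05, 6–7 patients per practice, drop-out 30%. Two-sided testing is not stated. It is assumed here because it reproduces the article's 47 (a one-sided test gives 39).

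**1. Unclustered size.** n = 2 × (1.96 + 1.645)² × (20/15)² = 46.2, so 47 per group. This matches the article.

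**2. First drop-out step.** 2 × 47 = 94, and 94 / 0.7 = 134.3. This matches the stated 134. Multiplying would give 94 × 1.3 = 122.2, which does not. The article therefore treats the drop-out rate as the fraction of enrolled patients who are lost.

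**3. Second drop-out step.**
- 66 × 1.3 = 85.8, so 86. This matches the article.
- 66 / 0.7 = 94.3, so 95 per group and 190 in total. This does not match.
- Remaining from 86 at 30% loss: 86 × 0.7 = 60.2 per group, about 6 short of 66 (9%).
- Largest loss at which 86 still leaves 66: 1 − 66/86 = 23.3%.

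**4. Clustering step.** Design effect = 1 + (m − 1) × 0.05, applied to 47:

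| Patients per practice (m) | Design effect | 47 × design effect | Divided by 0.7 |
|---|---|---|---|
| 6 | 1.25 | 58.75 (59) | 83.9 |
| 6.5 | 1.275 | 59.9 (60) | 85.6 |
| 7 | 1.30 | 61.1 (62) | 87.3 |
| 9 | 1.40 | 65.8 (66) | 94.0 |

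The stated cluster size gives 59–62 per group. In reverse, 66/47 = 1.404 and m = 1 + 0.404/0.05 ≈ 9.1. About 9 per practice is close to 172/20 = 8.6, but the article gives no such cluster size.

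**5. Power with 60.2 analysed per group.** Normal approximation: power = Φ(0.75 × √(n_eff/2) − 1.96), with n_eff = 60.2 / design effect.

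| Design effect | Source | n_eff | Power |
|---|---|---|---|
| 1.404 | implied by 66/47 | 42.9 | 93.5% |
| 1.30 | 7 per practice | 46.3 | 95.0% |
| 1.275 | 6.5 per practice | 47.2 | 95.4% |
| 1.25 | 6 per practice | 48.2 | 95.7% |

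For comparison, 66 analysed with design effect 1.404 gives n_eff = 47 and 95.3%. None of these figures includes a correction for the small number of practices.

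**The case against.** The strongest reply is that 86 may be right and 66 the slip. With 6.5 patients per practice and correct division, 47 × 1.275 / 0.7 = 85.6, which is also 86. The stated ICC and cluster size would then support 172 enrolled with about 95% power. This stands as a possible origin of the figure. It does not rescue the paragraph, which gives 66 as the requirement and presents 86 as that requirement allowing for 30% drop-out. The figures 66, 86 and 30% cannot all hold.

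A reader might go further and infer that the trial is underpowered, or that 190 is the correct target. The article supports neither. The 93.5% figure depends on a design effect worked back from 66, which implies a cluster size the article does not state. The figure of 190 takes 66 to be correct, and the text does not settle that. If 66 is the error, 190 would recruit about 18 patients more than needed.

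Two further points in the plan's favour stand, though the article gives nothing to size them. The sample size formula is an unadjusted comparison of two means, while the Data analysis section adjusts for the baseline outcome value, which usually adds precision. The analysis is also by intention to treat with replacement of missing values where applicable, so not every patient who drops out need be lost to the analysis.

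**Conclusion.** The paragraph is wrong as written, with a modest effect. It applies two drop-out formulas to one 30% rate, and its recruitment target leaves about 60 analysed patients per group against its own requirement of 66. Its 66 also disagrees with its own ICC and cluster size, which give 59–62.

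The consequence for power depends on which figure is the mistake. If 66 is the true requirement, 172 enrolled gives about 93–94% power, less than 2 points below the 95% claimed. If 6–7 per practice is right, 172 gives about 95.0–95.7% and the claim holds. Both results assume two-sided testing, the full 30% loss, and the normal approximation without a correction for few clusters. Power stays above 90% in every case examined, so this is a figure to correct and does not threaten the trial's validity.

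**What to change.** In Power calculation and sample size, apply division by 0.7 at both drop-out steps, state the cluster size and design effect behind the cluster-adjusted requirement, and make 66, 86, 172 and the cluster size agree. There are two consistent routes:

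- **If 66 is the true requirement:** state the cluster size behind it (about 9 per practice). Then either set the target at 95 per group (190 in total), or keep 172 and report about 60 analysed per group with about 93–94% power.
- **If 6–7 per practice is right:** replace 66 with about 60 per group. At 6.5 per practice, 60 / 0.7 = 85.7, so 86 per group and 172 in total can stay, with about 95% power.

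In either case, check the minimum of 20 practices against the chosen cluster size: 20 practices at 6–7 patients yield 120–140, whereas 172 needs 25–29 (172/7 = 24.6; 172/6 = 28.7).

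The cost is a few corrected sentences. Only the 190 option adds recruitment, 18 patients. Keeping 172 on the first route means stating a slightly lower power.

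### The minimum of 20 GPs does not follow from 6–7 patients per practice: that yield gives 120–140 patients, and the stated 172 would need 25–29 practices

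*Protocol article*

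**What the plan says.** All the relevant figures stand in one paragraph of the protocol article, under Power calculation and sample size.

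- The effect is 15 points on the 5A PACIC sum score, and the remaining inputs are given as "With a power of 95% and a standard deviation of 20 points [27".
- Before clustering and drop-out, "a sample size of *n* = 47 participating patients for each group was estimated to detect group differences".
- With drop-out only: "Given a 30% drop-out-rate, which is based on previous work of the ISAP, the overall sample size would comprise *n* = 134".
- With clustering: "interclass correlation coefficient of 5% from the cluster randomization the sample size would increase slightly to *n* = 66 patients per group". Drop-out then takes this to 86 per group.
- The number of practices follows: "We estimate that 6–7 patients per practice could be recruited into the trial. Therefore, the trial aims to enroll at least 20 GPs".
- The paragraph closes: "The overall sample will comprise 172 patients and not less than 20 GPs".

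The Data analysis section adds the test level: "The level of statistical significance will be set at *p* < 0.05 for all statistics". No other target for the number of GPs or practices appears in the article.

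**The concern.** The paragraph presents the GP minimum as a consequence of the recruitment yield, but the yield, the GP minimum and the patient total do not fit together. Practices are the units allocated in this trial, so the number of GPs is what the study team recruits against first. A team that met the printed minimum and achieved the printed yield would fall short of the printed sample, and on the plan's own assumptions short of the printed power. The patient total was inflated for drop-out. The GP minimum looks as if it was not.

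**Working it through.** **Inputs, all from the protocol article:** difference 15, SD 20, power 95%, α 0.05, ICC 0.05, drop-out 30%, 6–7 patients recruited per practice, 20 GPs, 172 patients. Sidedness is not stated. A two-sided test is assumed because it reproduces the printed 47 per group, whereas a one-sided test gives 39.

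**1. Reproducing the plan's figures**

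- Unadjusted: n = 2(1.960 + 1.645)² × (20/15)² = 46.2, so 47 per group, as printed.
- Drop-out only: 2 × 47/0.7 = 134.3, printed as 134.
- Design effect, DE = 1 + (m − 1) × 0.05: 1.25 at m = 6, 1.275 at m = 6.5, 1.30 at m = 7.
- Clustering and drop-out: 47 × DE/0.7 = 83.9, 85.6 and 87.3 per group. At m = 6.5 this rounds to 86 per group, or 172 in total.

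So 172 is consistent with the stated inputs, but the printed steps towards it are not:

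- 47 × 1.25 to 47 × 1.30 is 59–61, not 66. A figure of 66 implies DE = 66/47 = 1.40, or about 9 patients per practice.
- 86 is 66 × 1.3 = 85.8. Allowing for 30% loss means dividing by 0.7: 66/0.7 = 94.3, so 95 per group and 190 in total.

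**2. Practices against patients**

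- 20 × 6 = 120 and 20 × 7 = 140, which is 70–81% of 172. The shortfall is 172 − 140 = 32 to 172 − 120 = 52.
- Practices needed for 172: 172/7 = 24.6 and 172/6 = 28.7, so 25–29.
- Yield needed with 20 practices: 172/20 = 8.6.
- A possible source of 20 is the total before drop-out: 2 × 66 = 132, and 132/6.5 = 20.3. This is an inference; the arithmetic above does not depend on it.

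**3. Power if recruitment stopped at 20 practices with that yield**

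Analysed after 30% drop-out: 120 × 0.7 = 84 to 140 × 0.7 = 98, or 42–49 per arm. The effective number per arm is n/DE, and power = Φ(0.75 × √(n_eff/2) − 1.96), where 0.75 = 15/20.

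| Enrolled | DE taken at | DE | n_eff per arm | Power |
|---|---|---|---|---|
| 120 | enrolled size, 6 | 1.25 | 33.6 | 86.7% |
| 140 | enrolled size, 7 | 1.30 | 37.7 | 90.2% |
| 120 | retained size, 4.2 | 1.16 | 36.2 | 89.1% |
| 140 | retained size, 4.9 | 1.195 | 41.0 | 92.4% |

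**4. Comparison:** 172 patients in 25–29 practices leave 60.2 per arm. Power is then 95.1–95.8% with DE at enrolled size and 96.5–96.9% at retained size. The 95% is attainable at the stated yield with that number of practices.

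**The case against.** The strongest reply is that 20 is only a floor. Both mentions of the GP number are minimums, while 172 is stated without qualification. Nothing prevents the enrolment of 25–29 practices. A reader might infer that GP recruitment will close at 20, so that the plan as written cannot deliver its sample or its 95% power. The article does not support that: it contains no rule for closing GP recruitment and keeps 172 as the target. This part of the objection stands, and it makes the power loss conditional.

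The yield is also only an estimate. If 20 practices did supply 172 patients, at 8.6 each, power would be 93.9% (DE 1.38, enrolled size) to 95.7% (DE 1.25, retained size). The 95% therefore depends mainly on reaching 172. But 8.6 lies outside the plan's own 6–7, and that range is what the minimum is said to rest on.

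The planned model adjusts for the baseline outcome, which could recover power. The article gives no baseline correlation. If one assumes 0.3, the 87–92% becomes about 90–95%; with 0.5 it becomes about 94–98%. The printed 95% takes no such credit, so the like-for-like comparison is the unadjusted one.

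A reader might also take the phrase "may yield a minimum of 15 points difference prior to post-intervention" to mean that the trial was sized on a within-group change, and conclude that power is lower still. The same paragraph says that its 47 per group was estimated to detect group differences, so that reading is not established, and this point does not need it.

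None of these replies makes 20 × 6–7 equal 172.

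**Conclusion.** The GP minimum is wrong as written. At 6–7 patients per practice, 20 practices give 120–140 patients, and 172 needs 25–29 practices. This part is plain arithmetic on the printed figures.

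The effect on power is moderate and conditional. It arises only if recruitment stops at 20 practices with the stated yield and the planned 30% drop-out occurs. Power is then about 87–92% instead of 95%, for 15 points with SD 20, ICC 0.05, a two-sided 5% test, the normal approximation and no credit for baseline adjustment. With no drop-out, 120–140 patients would give 95.7–97.3%. Power stays above 80% throughout, so the trial is not invalidated.

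**What to change.** Restate the paragraph so that yield, practices, patients and power agree, in one of two ways:

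1. **Keep 172 patients and 95% power.** Correct the GP minimum to 25–29 practices at 6–7 patients each. This raises the printed floor by 5–9 practices and leaves the patient target unchanged.
2. **If 20 practices is the real limit.** State 120–140 enrolled patients and power of about 87–92%. This needs no further practices, but it is a smaller trial than the one now described, with lower stated power.

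In either case, reconcile the intermediate steps. Replace 66 per group with the 59–61 that ICC 0.05 gives at 6–7 patients, or state the cluster size that 66 assumes. Allow for drop-out by dividing by 0.7 rather than multiplying by 1.3. If 66 analysed patients per group is really required, the total becomes 190, and the practices needed become 28–32 (190/7 = 27.1, 190/6 = 31.7).

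The text change is confined to one paragraph. It is most useful before GP recruitment ends.
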